# Introduction

Coronary artery disease is a leading cause of death globally, nationally and locally. Currently in South Western Sydney Local Health District, Interventional Cardiologists perform Percutaneous Coronary intervention (PCI) procedure which opens coronary arteries that are narrowed or blocked by the build-up of atherosclerotic plaque. PCI may also be used to relieve symptoms of coronary heart disease or to reduce heart damage during or after a heart attack.  With new technology, engineering and training development, a technology-assisted percutaneous coronary intervention (PCI) device has the potential to increased procedural accuracy, reduce radiation exposure to participants and staff, improved ergonomics and reduce major adverse cardiac events. To date we are not aware of any randomised controlled trial data supporting this technology.

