## **Schedule of Events**

| **Exam/ Test/ Data Collection** | **Screening** | **Index**  **Procedure** | **Day 3/ discharge** | **Day 30**  **(±5 days)** | **EOS / Day 365**  **(±14 days)** |
| --- | --- | --- | --- | --- | --- |
| Informed consent | X | X |  |  |  |
| Medical history | X |  |  |  |  |
| Demographics | X |  |  |  |  |
| Vital signs including height, weight^1^ | X | X^6^ | X^6^ |  |  |
| Physical examination | X^1^ |  | X |  |  |
| 12 lead ECG | X^4^ |  | X |  |  |
| non-cardiac laboratory assessments | X |  | X |  |  |
| Cardiac enzymes | X^2^ |  | X^3^ |  |  |
| Inclusion/ exclusion criteria | X |  |  |  |  |
| Randomisation |  | X |  |  |  |
| PCI |  | X |  |  |  |
| Dosimeter reading |  | X |  |  |  |
| Fluoroscopy reading |  | X |  |  |  |
| Lesion assessment |  | x |  |  |  |
| Time of procedure |  | X |  |  |  |
| Contrast usage |  | X |  |  |  |
| Equipment usage |  | X |  |  |  |
| Concomitant medications | X | X | X | X | X |
| Adverse Events^5^ |  | X |  |  |  |
| Health care resource usage |  | X | X | X | X |
| Event Assessment |  | X | X^5^ | X^5^ | X^5^ |
| Complete Case Report Form | X | X | X | X | X |

^1^ Within 30 days of index procedure

^2^ Pre-procedure cardiac enzymes within 7 days of index procedure, if collected.

^3^ Post-procedure cardiac enzyme collection is left to the discretion of the investigator and shall be dictated by the participant’s clinical symptoms.

^4^ Post-procedure 12-lead ECG: it is recommended that an ECG be performed at the time of discharge but is not required for the protocol.

^5^ Related to procedure, intervention or Adverse Event of Special Interest (MACE)

^6^ height and weight only required at screening

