## **Inclusion Criteria**

- Age 18 to 85 years
- Participants with coronary artery disease with clinical indication for PCI
- Participant deemed appropriate for robotic-assisted PCI
- Able to provide a signed and dated informed consent form

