### Event Assessments

This study is not using any unregistered products therefore only serious adverse events that meet the MACE definition will be reported from visit 2 until the end of study visit (visit 5). Event Assessments will be reviewed by the End-Point Adjudication Committee.

**Major Adverse Cardiac Event (MACE):** MACE is defined as cardiac death, Q-wave or non Q-wave myocardial infarction (MI), or clinically driven target vessel revascularization (TVR) by percutaneous or surgical methods.

**Cardiac Death:** Death due to cardiac causes. If the cause of death cannot be determined, it will be categorized as cardiac.

Myocardial Infarction (Protocol Definition):

Clinically relevant MI after coronary revascularization will be defined by the 4^th^ Universal Definition of PCI related MI. Events as defined by the Society for Cardiovascular Angiography and Interventions definition for periprocedural MI will also be recorded.

The 4th Universal Definition of PCI related MI defines:

- Participants with normal baseline cardiac biomarkers
  - Cardiac troponin (cTN) >5x the 99^th^ percentile of upper reference limit (URL)
- Participants with elevated baseline cardiac biomarkers
  - Rise in post procedure cTN by >20% and be at least >5x 99^th^ percentile of URL AND
  - At least one of the following
    - New ischaemic ECG changes
    - Development of new pathological Q waves
    - Imaging evidence of new loss of viable myocardium or new regional wall motion abnormality in a pattern consistent with an ischaemic aetiology
    - Angiographic findings consistent with a procedural flow limiting complication such as coronary dissection, occlusion of a major epicardial artery or a side branch occlusion/thrombus, disruption or collateral flow or distal embolisation

The Society for Cardiovascular Angiography and Interventions definition for periprocedural MI defines:

- Participants with normal baseline cardiac biomarkers
  - CK-MB >10x upper limit normal (ULN) or cTn (I or T) >70x ULN, or
  - CK-MB >5x ULN or cTn >35x ULN plus new Q-waves in >2 contiguous leads or LBBB
- Participants with elevated baseline cardiac biomarkers
  - Baseline biomarkers are stable or falling:
    - CK-MB >10x ULN or cTn (I or T) >70x ULN of **most recent pre-procedure level**, or
    - CK-MB >5x ULN or cTn >35x ULN of **most recent pre-procedure level** plus new Q-waves in >2 contiguous leads or LBBB

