  - Baseline biomarkers have not been shown to be stable or falling: CK-MB (or cTn) rises by an absolute increment equal to those recommended above plus new ST-segment elevation or depression plus signs consistent with a clinically relevant MI, such as new onset or worsening heart failure or sustained hypotension.

**Target Vessel Revascularization (TVR):** Ischemia-driven repeat percutaneous intervention of the target vessel or bypass surgery of the target vessel. A TVR will be considered as ischemia-driven if the target vessel diameter stenosis is
[figure not shown]
≥50% and any of the following are present:

- A positive functional study corresponding to the area served by the target vessel.
- Ischemic ECG changes at rest in a distribution consistent with the target vessel.
- Ischemic symptoms referable to the target lesion.

**In-Hospital MACE:** MACE that occurs within 72 hours of the procedure or prior to hospital discharge, whichever occurs first, in a participant treated with the CorPath GRX System.

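### The MI rule for raised baseline troponin sets no condition on the pre-PCI trend, so an index infarct still evolving can be scored as MACE and clinical failure

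*Protocol*

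**What the plan says.** Section 7.7.2 (Event Assessments) fixes the governing definition: "Clinically relevant MI after coronary revascularization will be defined by the 4^th^ Universal Definition of PCI related MI". Section 2.2.1 (Clinical Success) says the same and prints the same criteria. For a raised baseline both sections require "Rise in post procedure cTN by >20% and be at least >5x" the 99th percentile of the upper reference limit, and at least one of four supporting findings. Two of these are "New ischaemic ECG changes" and "Development of new pathological Q waves". The third is imaging evidence of new myocardial loss or wall motion abnormality. The fourth is an angiographic procedural complication.

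Both sections also print the SCAI definition, which is recorded for additional analysis. It treats stable or falling baselines separately from the rest and has its own branch for the latter: "Baseline biomarkers have not been shown to be stable or falling: CK-MB (or cTn) rises by an absolute increment equal to those recommended above", together with new ST change and clinical signs.

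Appendix A, under the label of the protocol's own MI definition, prints only the SCAI criteria, including that split.

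On the population, section 4.1 admits "Participants with coronary artery disease with clinical indication for PCI". The single exclusion in section 4.2 concerns suitability for robotic PCI. The Introduction notes that "PCI may also be used to relieve symptoms of coronary heart disease or to reduce heart damage during or after a heart attack". On sampling, footnote 2 of the Schedule of Events reads "Pre-procedure cardiac enzymes within 7 days of index procedure, if collected". Clinical success in 2.2.1 requires the absence of in-hospital MACE.

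**The concern.** In a participant treated during an acute infarction, troponin may still be climbing when PCI starts. A later value more than 20% higher then says little about the procedure. Three of the four supporting findings (ECG, Q waves, imaging) are not tied to a procedural cause in the printed text, and an evolving infarct can produce each of them. The rule can therefore count the disease that led to the PCI as harm from the PCI.

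One such misclassification counts twice: in MACE, the main safety measure, and in clinical success, an effectiveness measure. The protocol recognises the difficulty, because the SCAI text in the same section handles it, but the definition that governs MACE in 2.2.1 and 7.7.2 does not.

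**Working it through.** The plan gives no figure to reproduce here. The check is of the text and its logic, followed by an illustration on stated assumptions.

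**1. The definitions side by side (raised baseline)**

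| Place | Role | Condition on pre-PCI trend |
| --- | --- | --- |
| 2.2.1 and 7.7.2, 4th Universal Definition as printed | defines MI within MACE | none |
| 2.2.1 and 7.7.2, SCAI | recorded additionally | yes, two branches |
| Appendix A, SCAI criteria | labelled as the protocol's MI definition | yes, two branches |

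**2. A test case.** Assume troponin of 8x and then 20x the reference limit before PCI, 40x after PCI, and new Q waves from the index infarct. Treat the two definitions' reference limits as equal.

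- Rule as printed: the rise is (40 − 20)/20 = 100%, above 20%; 40x is above 5x; a supporting finding is present. An MI is scored.
- Same rule, but with a precondition that the pre-PCI change is at most 20%: (20 − 8)/8 = 150%, so the baseline was rising and no MI is scored by this route.
- SCAI branch for unsettled baselines: the increment is 40 − 20 = 20x, below both 70x and 35x. No MI is scored.
- Rule as printed without any supporting finding: no MI is scored. A troponin rise alone is not enough.

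**3. Is the trend known?** Footnote 2 of the Schedule asks for enzymes within 7 days, where collected. No serial values are required, so a participant may have one raised value of unknown trend.

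**4. Size, on assumptions only.** Let a be the share of participants with troponin rising at PCI, and m the share of those who meet the rule through infarct evolution. The protocol gives neither. False events per arm of 150 = 150 × a × m.

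- a = 10%, m = 5%: 150 × 0.10 × 0.05 = 0.75
- a = 30%, m = 10%: 150 × 0.30 × 0.10 = 4.5
- a = 50%, m = 20%: 150 × 0.50 × 0.20 = 15

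The range is wide enough to run from negligible to important.

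**5. Effect on the comparison.** Suppose a false event occurs with the same probability f = a × m in both arms, independently of true events. An arm with true risk p then shows p + (1 − p)f. The observed risk difference is (p1 − p0)(1 − f). With f from 0.10 × 0.05 = 0.005 to 0.50 × 0.20 = 0.10, the difference shrinks by 0.5% to 10% of itself. The risk ratio moves towards 1, because both risks gain nearly the same amount, and the extra events add variance.

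**The case against.** The strongest reply is that Appendix A already contains the split, so the gap vanishes if Appendix A governs. That stands as far as it goes, but 2.2.1 and 7.7.2 are explicit that the 4th Universal Definition governs. The contradiction has to be resolved, and resolving it in favour of those sections leaves the gap open.

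Second, the definition is adopted by reference, and the full source may deal with the baseline trend. That cannot be checked from the protocol. The criteria printed for sites and adjudicators carry no such condition.

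Third, section 10.2 provides an independent committee with laboratory reports and ECGs from before and after the procedure, and the supporting findings must be new. This helps, but no instruction covers an evolving index infarct, and the rule taken literally tells the committee to count it. The additional SCAI recording gives a trend-aware view but does not change MACE or clinical success.

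Fourth, footnote 3 of the Schedule and section 7.2.8 leave post-procedure enzymes to clinical judgement, although section 7.3 lists them without that limit. A rise that is not measured cannot be scored. This stands and limits how often the rule can be met.

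Three stronger readings are tempting:

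- *False events would swamp the true ones.* A reader might take the 97.6% clinical success in section 1.3.2 and expect 150 × 0.024 = 3.6 failures per arm. That figure is a rate over treated lesions in a cited study, not over participants here, and the number of false events is unknown.
- *The trial therefore cannot tell whether robotic PCI changes periprocedural MI.* The sample size in section 8.1 rests on patient radiation, and SCAI events are recorded as well. The wording of this rule is not what decides that question.
- *The error falls only on the robotic arm.* The in-hospital MACE entry in 7.7.2 and Appendix A mentions only CorPath-treated participants. The Summary's MACE measure has no such limit, and section 2.4 covers both treatments. This is a separate inconsistency to reconcile, not evidence of one-sided bias.

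**Conclusion.** The point holds as a defect in the printed rule. For raised baselines, sections 2.2.1 and 7.7.2 allow an evolving index infarct with one supporting finding to be counted as MACE and, in the in-hospital window, as clinical failure. Appendix A conflicts with them on exactly this matter.

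Its size is not derivable. The 0.75 to 15 events per arm above rests wholly on assumed shares and takes no account of enzymes not being drawn. If the error is equal between arms, the consequence is noise and a diluted relative comparison, with little change in the risk difference. It is worth correcting because the correction is cheap and both affected measures are prominent, not because a large bias has been shown.

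**What to change.** 1. Reconcile 2.2.1 and 7.7.2 with Appendix A, so that one MI definition governs MACE throughout.
2. Apply the 20% rise rule only where the last pre-PCI troponin values were stable or falling, and state what counts as stable.
3. For raised baselines that are rising or of unknown trend, including those with a single value, have the adjudicators decide against pre-PCI ECG and imaging, blinded to arm where possible. They choose between a procedural MI (for example with an angiographic procedural complication) and *evolution of index MI*, which is not a MACE.
4. Report MACE and clinical success also with the SCAI definition already being recorded, as a sensitivity analysis.
5. Capture in the CRF the pre-PCI troponin values and times already in the hospital record.

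Making the strict SCAI branch the only route to an MI for every other raised baseline is not advised. It would create a hybrid of two definitions and drop true events where only one baseline value exists.

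Cost: a wording amendment with ethics committee approval, an adjudication instruction, a few CRF fields and one extra analysis. No additional tests are needed. The downside is that some true periprocedural MIs on a rising or unknown baseline will be missed, in both arms.

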# Corindus Randomised Controlled Trial Summary

| **Title:** | Percutaneous Coronary Intervention using assisted robotic technology: a randomised controlled trial |
| --- | --- |
|  |  |
| **Short Title:** | **P**CI using **A**ssisted **R**obotic **T**echnolog**Y** trial: the **PARTY** trial |
|  |  |
| **Study Description:** | Coronary artery disease is a leading cause of death globally, nationally and locally. Currently in South Western Sydney Local Health District Interventional Cardiologists perform Percutaneous Coronary intervention (PCI) procedure which opens coronary arteries that are narrowed or blocked by the build-up of atherosclerotic plaque. PCI may also be used to relieve symptoms of coronary heart disease or to reduce heart damage during or after a heart attack.  With new technology, engineering and training development, a technology-assisted percutaneous coronary intervention (PCI) device has the potential to increase procedural accuracy, reduce radiation exposure to participants and staff, improved ergonomics, and reduce major adverse cardiac events. To date we are not aware of any randomised controlled trial data supporting this technology |
| **Study Design:** | This is a randomized controlled trial of the CorPath GRX System versus standard PCI to compare participant outcomes at 72 hours post-procedure or hospital discharge, day 30 and 1 year. |
|  |  |
| **Study Objective:** | This study will assess the safety, effectiveness including the clinical and technical performance and cost analysis of technology-assisted PCI versus standard PCI performed by a cardiologist in a randomised controlled trial. |
| **Effectiveness Performance Measures:** | **Clinical Success:**  Less than 30% residual stenosis (visual estimate) post PCI, without in-hospital major adverse coronary events (MACE).  **Technical Success:**  Defined as successful completion of the PCI absent ***unplanned*** conversion to manual operation of guidewires or balloon/stent catheter or inability to navigate vessel anatomy or poor guide catheter support. |
|  |  |
| **Safety Measures:** | **Major Adverse Cardiac Event (MACE):**  MACE that occurs within 72 hours of the procedure or prior to hospital discharge, whichever occurs first, day 30 and 1 year  **Serious Adverse Events:**  All Serious Adverse Events (SAEs) from the start of the PCI procedure until the end of the study will be summarized. |
| **Cost Measures:** | Total procedural cost of PCI at day 30 and 1 year |

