### 2.2.1 Clinical Success

Defined as less than 30% residual stenosis (visual estimate) post PCI in the lesion(s) treated, without in-hospital MACE.

MACE is defined as cardiac death, clinically relevant MI after coronary revascularization (Q-wave or non-Q-wave myocardial infarction), or clinically driven target vessel revascularization (TVR) by PCI or CABG. Clinically relevant MI after coronary revascularization will be defined by the 4^th^ Universal Definition of PCI related MI. Events as classified by the Society for Cardiovascular Angiography and Interventions definition for periprocedural MI will also be recorded for additional analysis.

The 4th Universal Definition of PCI related MI defines:

- Participants with normal baseline cardiac biomarkers
  - Cardiac troponin (cTN) >5x the 99^th^ percentile of upper reference limit (URL)
- Participants with elevated baseline cardiac biomarkers
  - Rise in post procedure cTN by >20% and be at least >5x 99^th^ percentile of URL AND
  - At least one of the following
    - New ischaemic ECG changes
    - Development of new pathological Q waves
    - Imaging evidence of new loss of viable myocardium or new regional wall motion abnormality in a pattern consistent with an ischaemic aetiology
    - Angiographic findings consistent with a procedural flow limiting complication such as coronary dissection, occlusion of a major epicardial artery or a side branch occlusion/thrombus, disruption or collateral flow or distal embolisation

The Society for Cardiovascular Angiography and Interventions definition for periprocedural MI defines:

- Participants with normal baseline cardiac biomarkers
  - CK-MB >10x upper limit normal (ULN) or cTn (I or T) >70x ULN, or
  - CK-MB >5x ULN or cTn >35x ULN plus new Q-waves in >2 contiguous leads or LBBB
- Participants with elevated baseline cardiac biomarkers
  - Baseline biomarkers are stable or falling:
    - CK-MB >10x ULN or cTn (I or T) >70x ULN of **most recent pre-procedure level**, or
    - CK-MB >5x ULN or cTn >35x ULN of **most recent pre-procedure level** plus new Q-waves in >2 contiguous leads or LBBB
  - Baseline biomarkers have not been shown to be stable or falling: CK-MB (or cTn) rises by an absolute increment equal to those recommended above plus new ST-segment elevation or depression plus signs consistent with a clinically relevant MI, such as new onset or worsening heart failure or sustained hypotension.

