## **Safety Measures**

Several safety-based measures will also be utilized to confirm the overall safety of procedures involving the CorPath GRX System and standard of care. These measures include:

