### Major Adverse Cardiac Events (MACE)

MACE will be measured at each visit of the study.

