## **Cost Measures**

The cost of standard PCI versus technology-assisted PCI will be measured using equipment utilisation and post procedural length of stay until discharge. The costs of these two measurements will be compared and summarized.

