## **Day only PCI patients**

Some patients will be suitable for same day discharge as their PCI procedure. In this instance, they will be asked to return the next day to the cathether laboratory clinic for a medical review as detailed in Section 7.3.

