# Data Management, Statistical Analysis and Record Keeping

## **Statistical Methods**

This is a double-arm, open-label, randomized controlled trial of the CorPath GRX System designed to evaluate the safety and effectiveness of the clinical and technical performance of the CorPath GRX System in the delivery and manipulation of coronary guidewires and stent/balloon catheters, and remote manipulation of guide catheters for use in PCI in comparison to standard of care. The analysis of data collected as part of the RCT will include, but may not be limited to, the Objectives and Measures outlined in Section 3.0 of this protocol. Continuous variables will be summarized using the number of observations, mean, standard deviation, median, min and max values. Categorical variables will be summarized with the number and percent in each category out of the number observed. Two-sided 95% confidence intervals may be calculated and two-sided p-values < 0.05 will be considered statistically significant.

The outcome of patient radiation exposure will be analysed using variance (ANOVA). As each participant may have multiple lesions, the outcome of clinical success at day 3 will be analysed using a two level multilevel models. Logit link will be used with a binomial distribution and restricted maximum likelihood (REML) will be used for estimation. Predictor variables in the models will include treatment group.

Technical success will analysed with Fisher’s exact test, comparing the proportion of participants with technical success between the two groups. Logistic regression will be used to compare technical success accounting for lesion complexity. For all other secondary outcomes, continuous outcomes will be measured using independent t-test (or non-parametric alternative depending on distributional assumptions), and categorical outcomes analysed by Fisher’s exact test. For outcomes measured repeatedly over time, multilevel models with an appropriate link functions will be used for analysis.

All statistical analyses will be performed using SAS software (version 9.4) or other widely accepted statistical or graphical software.

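### In-hospital MACE is defined only for participants treated with CorPath, which contradicts the arm-neutral MACE text elsewhere and, if applied literally, biases clinical success against the device

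*Protocol*

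**What the plan says.** Section 2.2.1 of the protocol sets the effectiveness outcome of clinical success: "Defined as less than 30% residual stenosis (visual estimate) post PCI in the lesion(s) treated, without in-hospital MACE". The summary states it in nearly the same way.

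The term in-hospital MACE is defined in section 7.7.2 (Event Assessments) and again in Appendix A. Each definition gives a window ending at 72 hours or discharge and closes with "whichever occurs first, in a participant treated with the CorPath GRX System". The protocol defines the term nowhere else.

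Section 8.1 (Statistical Methods) analyses clinical success at day 3 with a two-level logit model and adds: "Predictor variables in the models will include treatment group". It is therefore a between-arm comparison.

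Other text on MACE carries no arm restriction:

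- The summary's safety measure reads "MACE that occurs within 72 hours of the procedure or prior to hospital discharge, whichever occurs first, day 30 and 1 year".
- Section 2.4 says the safety measures address the "overall safety of procedures involving the CorPath GRX System and standard of care".
- Section 2.4.1 says "MACE will be measured at each visit of the study".
- Section 3.1 follows every enrolled participant through the same early window.
- Section 7.7.2 itself has MACE reported from visit 2 to visit 5, without reference to arm.

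**The concern.** A composite outcome compared between randomised arms must be scored by one rule. Here, one component of failure is a named term whose only definitions exclude anyone not treated with CorPath. Under those words a standard-PCI participant cannot have an in-hospital MACE. Such a participant who has an MI before discharge, with residual stenosis under 30%, remains a clinical success, whereas the same course after CorPath is a failure. The contrast would then mix any device effect with an effect of the definition, always in the direction that harms the device.

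There is a second fault in the same clause. It refers to treatment received, not to the arm assigned. Section 6.0 keeps in the study those who never proceed to PCI and those who convert from robotic to manual PCI. Someone randomised to CorPath but never treated with it falls outside the definition, and the status of partial robotic use is unclear.

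**Working it through.** **Texts side by side.** The two definitions agree with each other and restrict the term to CorPath. The summary gives the same window with no restriction, and sections 2.4, 2.4.1, 3.1 and 7.7.2 (reporting) are arm-neutral. The protocol contradicts itself, and the restricted version is the one attached to the term used in clinical success.

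**The plan's own figure.** The only powered outcome is patient radiation exposure (section 8.1). A 20% reduction from 1284 mGy is 0.20 × 1284 = 256.8 mGy. The pooled SD is √[(180² + 142.83²)/2] = 162.5. With 150 per arm and two-sided 5%, power is 1.000 to three decimals, which agrees with the stated figure above 99%. In-hospital MACE does not enter this calculation.

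**Inputs for the size of the bias.**

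- 150 per arm, from section 8.1.
- In-hospital MACE rate q: not in the protocol. Assumed to be 1%, 2%, 5% or 10%, equal in both arms.
- Residual-stenosis success s: not in the protocol for this trial. Assumed to be 97.6% (borrowing the clinical success figure cited in section 1.3.2) or 99%.
- The two components are taken as independent, with no true difference between arms.

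**Formulas.** Under the literal definition, CorPath success = s(1 − q) and control success = s. The false difference is −sq, which is close to −q. Under a common definition both arms have s(1 − q) and the difference is 0. Worked example: s = 0.976 and q = 0.05 give 0.976 × 0.95 = 92.7% against 97.6%, a difference of −4.9 points.

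The last two columns give the exact probability that a two-sided 5% Fisher test rejects with 150 against 150.

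| s | q | CorPath success | Control success, literal | Difference (points) | Rejection, literal | Rejection, common definition |
|---|---|---|---|---|---|---|
| 97.6% | 1% | 96.6% | 97.6% | −1.0 | 3.3% | 2.0% |
| 97.6% | 2% | 95.6% | 97.6% | −2.0 | 8.0% | 2.3% |
| 97.6% | 5% | 92.7% | 97.6% | −4.9 | 39.7% | 2.9% |
| 97.6% | 10% | 87.8% | 97.6% | −9.8 | 89.5% | 3.4% |
| 99% | 1% | 98.0% | 99% | −1.0 | 2.2% | 1.2% |
| 99% | 2% | 97.0% | 99% | −2.0 | 9.6% | 1.9% |
| 99% | 5% | 94.1% | 99% | −5.0 | 55.3% | 2.7% |
| 99% | 10% | 89.1% | 99% | −9.9 | 96.5% | 3.4% |

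The expected number of control-arm MACE not counted is 150q: 1.5, 3, 7.5 and 15 for the four rates.

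Fisher's test is a participant-level stand-in. The planned analysis of clinical success is the two-level logit model, so the rejection rates are indicative only. The difference −sq does not depend on the choice of test.

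**The case against.** The strongest reply is that the intent is plainly arm-neutral. MACE is defined, measured and reported in everyone, and the summary gives the window without the clause. On this view an analyst would ignore the restriction. Most of this stands. A reader might infer that the trial will score its arms by different rules, but the documents do not support that as a fact: the bias is conditional on literal use, and control-arm events are still collected. What the reply does not do is remove the contradiction. Adjudicators and programmers work from definitions, and an analysis plan citing these would inherit the clause. Section 8.1 also calls the trial open-label, so choosing a reading once events and allocation are known would be open to challenge.

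The size is also assumption-driven. At a 1% MACE rate the rejection probability stays below 5%, and the larger figures need rates that the protocol does not give. This stands in full.

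Three stronger readings are tempting and do not hold:

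- **That the lead outcome is damaged.** Clinical success is listed first, but the protocol does not designate it as lead or primary. The powered outcome is radiation exposure.
- **That the window itself is biased**, because it closes at discharge, "Some patients will be suitable for same day discharge as their PCI procedure", and the cost measures compare "post procedural length of stay until discharge". The window is stated consistently in the summary, section 3.1, section 7.7.2 and Appendix A, and it is the same for both arms. No figure in the protocol shows that discharge timing differs by arm.
- **That a fixed 72-hour window would be an easy repair.** It would change the endpoint. Next-day review is planned only for same-day discharges, so someone leaving on day 1 or 2 has no planned contact after the discharge assessment until day 30. Post-procedure enzymes after discharge would be discretionary.

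**Conclusion.** The concern holds as an error of wording with a known direction. The only two definitions of in-hospital MACE restrict it to CorPath-treated participants, against the rest of the protocol, and the term feeds an outcome compared by arm. If applied as written, the comparison is biased against the device by approximately the in-hospital MACE rate: about 1, 2, 5 or 10 points at assumed rates of 1%, 2%, 5% or 10%. False rejection then ranges from about 2–3% at the lowest rate to about 90–96% at the highest, given residual-stenosis success of 97.6% to 99%, independent components and Fisher's test as a stand-in. These figures show what literal use could do; they do not forecast what the trial will do. The clause also ties event status to treatment received rather than assigned arm. The sample-size justification is not affected.

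**What to change.** In section 7.7.2 and in Appendix A, delete everything after the comma in "whichever occurs first, in a participant treated with the CorPath GRX System". The existing window (72 hours or discharge, whichever is earlier) then applies identically to both arms and matches the summary. Add that in-hospital MACE, and hence clinical success, is analysed by randomised arm, including participants who convert from robotic to manual PCI.

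The cost is the same small edit in two places, plus one clarifying sentence, in a protocol amendment, ideally before anyone looks at outcomes by arm. No new visit, test or data item is needed, because MACE is already collected and adjudicated in both arms. The sample size does not change.
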